###### 2.4.2.1.2 Strategies to improve adherence to interventions

Before the surgery, explain the exact effects of the electrical stimulation–related therapies to the patients who have signed the informed consent form to reduce their preoperative fear and tension.

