The auricular branch of the vagus nerve (ABVN) is the vagus nerve’s only superficial branch, distributed to the auricle, auricular concha, tragus, and other areas. A meta-analysis involving 17 RCTs indicates that 75% of localized auricular acupuncture stimulation primarily targets regions innervated by the ABVN (5). TaVNS exerts modulatory effects on the brain by stimulating the ABVN, thereby influencing the central nervous system (6). In recent years, significant progress has been made in the treatment of chronic pain, epilepsy, and severe depression (7). It has been shown that electrical stimulation of the vagus nerve in the patient’s ear area reduces the frequency of seizures in drug-resistant epilepsy (8), and is thought to have a significant effect on autonomic modulation, which can be effective in controlling pain and sedative effects. In terms of neurophysiology, taVNS activates brainstem centers by stimulating the afferent fibers of the ABVN, thereby enhancing efferent parasympathetic nerve activity. This process increases acetylcholine release onto the sinoatrial node of the heart, leading to reduced heart rate and increased vagally-mediated HRV (9). The precise mechanisms and effects of taVNS are not yet fully understood. Preliminary research suggests that taVNS may stimulate the cholinergic anti-inflammatory pathway, resulting in reduced production of pro-inflammatory cytokines (e.g., IL-1β, IL-6), thereby exerting anti-inflammatory effects (10). It may also modulate noradrenergic activity in the locus coeruleus (LC), consequently influencing the body’s autonomic nervous system (11). Furthermore, no consensus has been reached regarding the optimal stimulation duration, the most effective sites for stimulation, or the ideal stimulation parameters (12).

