### 2.3 Sample size calculation

This study is a randomized controlled trial aiming to compare the effects of TENS and taVNS in foraminoscopy. According to relevant research, with the VAS as the primary outcome indicator, the standard deviation of taVNS is 2.5, and that of TENS is 3.0. Calculated using PASS software, the minimum sample size required for each group is 121. Considering a dropout rate of 10%–15%, to ensure the statistical power and the reliability of the results, the final sample size of each group is adjusted to 136 people. Each subgroup was allocated 32 participants, and a total of 272 participants are recruited.

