#### 2.4.2 Intervention description

Based on a systematic review and related studies (23), each group receives 30-min corresponding stimulation or placebo intervention before surgery. The current intensity is adjusted to the maximum tolerance of the patient, the pulse width is fixed at 200 μs, and the frequency is fixed at 30 Hz. When patients with severe pain cannot tolerate it, oliceridine fumarate injection is supplemented to the subjects. The supplementary standard is: a single dose of 0.35 mg–0.50 mg, intravenous injection, and the dosing interval is not less than 6 min.

•TENS Group: Electrodes are placed at the bilateral Neiguan and Hegu acupoints of the subjects. Hegu (LI4): Located on the dorsum of the hand, between the 1st and 2nd metacarpal bones, at the midpoint of the radial side of the second metacarpal bone. Neiguan (PC6): Located on the palmar aspect of the forearm, 2 cun proximal to the transverse wrist crease, between the tendons of the palmaris longus and the flexor carpi radialis muscles.•TaVNS Group: Electrodes are placed at the bilateral tragus of the subjects.

Each stimulation group was further subdivided into following stimulation modes:

•Continuous Wave Group: Given 30-min continuous electrical stimulation.•Intermittent Wave Group: Subjects receive 30-min intermittent electrical stimulation (stimulate once every 15 s, with an interval of 5 s).•Dense-Sparse Wave Group: Subjects receive 30-min variable–frequency electrical stimulation (sparse wave 6 Hz, dense wave 30 Hz).•Control Group: Electrode patches are placed but not energized, making the patients psychologically believe that they have received stimulation.

The experimental process is shown in Figure 1.

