## 4 Discussion

HRV refers to the variation in time intervals between consecutive heartbeats and is mainly controlled by the cardiac autonomic nerves. It has been widely recognized as an effective indicator for evaluating autonomic nerve function.

The application of TENS and taVNS represents an emerging analgesic, sedative, and neuromodulatory strategy during foraminoscopy. These two non-pharmacological, minimally invasive modulation techniques are considered potentially beneficial for optimizing perioperative management, though their effects require cautious evaluation. Both modalities deliver electrical currents via stimulators, constituting a primary source of electromagnetic interference. Consequently, they are contraindicated in patients with implantable cardioverter defibrillators (ICDs), with interference levels demonstrating significant correlation to stimulation parameters that necessitate strict control (28). Additionally, substantial challenges exist in parameter selection due to individual variability in:neural sensitivity to stimulation, stimulation tolerance thresholds, psychological factors. Electrode placement for TENS should avoid surgical fields to prevent contamination. Notably, high-quality clinical studies investigating TENS and taVNS applications during MAC for transforaminal endoscopy remain limited. This study aims to provide novel clinical data in this domain.

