Some studies have shown that a higher HRV is usually associated with a healthy state, stronger adaptability, and a lower disease risk (29); while a lower HRV is related to anxiety, stress, cardiovascular diseases, etc (24). In addition, Billman (30) found that HRV is also related to the body’s stress response, and the cardiac parasympathetic nerve activity is the main part of HRV. In this paper, the regulation of cardiac vagus nerve and parasympathetic nerve is quantitatively and dynamically evaluated by analyzing the frequency domain, time domain, and non-linear analysis methods of HRV. The VAS is a commonly used subjective assessment tool, which is widely used for various subjective experiences such as pain and anxiety. By using HRV and VAS together, this study comprehensively evaluates the intervention effect from both physiological and psychological dimensions. The BIS value is an important tool for assessing the depth of anesthesia during the operation. Together with the sedation scale (MOAA/S) and Ramsay sedation scale, the intraoperative state of patients can be evaluated in detail to ensure efficient evaluation.

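### Patients in every arm, sham included, are to be told the exact effects of a treatment whose effects the protocol calls uncertain; a neutral, identical briefing should replace this

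*Protocol article*

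**What the plan says.** Section 2.4.2.1.2, on adherence, instructs staff before surgery to "explain the exact effects of the electrical stimulation–related therapies to the patients who have signed the informed consent form". The stated purpose is "to reduce their preoperative fear and tension". The instruction covers all consented patients and does not set controls apart.

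Other sections bear on it:

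- **Introduction:** "The precise mechanisms and effects of taVNS are not yet fully understood".
- **Section 4 (Discussion), on TENS and taVNS together:** the techniques are potentially beneficial, "though their effects require cautious evaluation".
- **Section 2.3:** the sample size is calculated "with the VAS as the primary outcome indicator".
- **Section 4:** "The VAS is a commonly used subjective assessment tool".
- **Section 2.4.2, active arms:** "The current intensity is adjusted to the maximum tolerance of the patient".
- **Section 2.4.2, controls:** "Electrode patches are placed but not energized, making the patients psychologically believe that they have received stimulation".
- **Section 2.2:** patients are described as unaware of their group. Pads are placed at both the ear and the acupoints in everyone, and each of the two main groups has its own control group.

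**The concern.** There are two difficulties, one of consistency and one of design.

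The first is that the trial exists to find out what these techniques do during foraminoscopy. The article says elsewhere that this is not settled. An instruction to state exact effects asks staff to present as known what the trial is meant to test.

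The second is that a statement of effect given before treatment can change how a patient rates pain. The VAS is self-rated and drives the sample size. The briefing is also meant to lower fear and tension, and the Discussion itself links low heart rate variability to anxiety and stress. The message is therefore aimed at a state that more than one primary indicator may reflect. If patients could work out their arm, the message could act unequally across arms, and part of an observed difference could then come from the briefing.

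**Working it through.** The plan gives no figure on this point, so the check sets the sections side by side and then asks when a common briefing can affect a comparison.

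**1. Consistency.** Section 2.4.2.1.2 requires exact effects to be explained. The Introduction says of taVNS that mechanisms and effects are not fully known. The Discussion asks for caution about the effects of both techniques. The conflict with the Introduction is direct but covers taVNS only; the Discussion extends the tension to TENS.

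**2. If blinding holds.** Let *e* be the change in VAS that the briefing causes, the same in every arm. Then

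(active + *e*) − (sham + *e*) = active − sham.

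The difference is unchanged. In practice a larger sham response may leave less room for an active effect to show, which would work against finding one.

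**3. If patients can tell whether they are stimulated.** Section 2.4.2 supplies the cue: current set at the limit of tolerance against pads with no current. Let *e_A* be the shift in patients who know they are stimulated and *e_S* the shift in those who believe they are not. The active-versus-sham difference is then off by *e_A* − *e_S*. The documents give neither term.

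**4. If patients can also tell where.** Pads lie at both sites in everyone, but current flows at one. Let *e_V* and *e_T* be the shifts in stimulated taVNS and TENS patients. The two control groups are physically alike (pads at both sites, no current), so they share one shift *e_S*. Take four equal subgroups per main group, three active and one control, and assume controls are included in the main comparison. Then

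bias (taVNS − TENS) = (3/4 *e_V* + 1/4 *e_S*) − (3/4 *e_T* + 1/4 *e_S*) = 3/4 (*e_V* − *e_T*).

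The sham shift cancels. Bias in the main comparison needs *e_V* ≠ *e_T*, that is, different expectations for ear and arm. The documents do not say that patients are told different things about the two sites.

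**5. Can it be sized?** No. Section 2.3 gives SDs of 2.5 and 3.0 and 121 per group, but neither the target difference nor the power. Assuming 80% power (two-sided 0.05, multiplier 2.802), the detectable difference would be √((2.5² + 3.0²)/121) × 2.802 = √(15.25/121) × 2.802 = 0.995 points. That figure belongs to taVNS versus TENS. Active versus sham is a different contrast in smaller subgroups (32 each as stated), so 0.995 is no yardstick for the shift in step 3.

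**The case against.** The strongest reply is that the instruction is one message for everyone, and a message common to all arms does not bias a randomized comparison. It may even shrink the active-versus-sham difference. The real weakness of the sham is the contrast between felt and unfelt current in Section 2.4.2, which exists whatever patients are told and which a new script would not remove. The word exact may simply be loose, patients already hear the procedures in detail at consent (Section 2.1.3), and a briefing script is the kind of detail an article leaves to the full protocol.

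Most of this stands. The missing script is not the point; the point is the instruction that is printed. The sham contrast is the larger threat to blinding, and the briefing can only compound it by giving patients something to attach to what they feel.

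A reader might infer more than the text allows:

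- **That sham patients are told what they should feel.** The text speaks of effects, not sensations.
- **That the briefing differs by site, or passes on a belief that taVNS is better.** Section 3.5 and the Discussion state expected results; nothing says that staff convey them to patients.
- **That the active-versus-sham difference is necessarily inflated.** That requires failed blinding, and without it the effect may go the other way.
- **That the Discussion's report of insufficient evidence for TENS contradicts the briefing.** It concerns neuropathic pain, and the same paragraph cites benefit after hernia repair.
- **That the bias is a stated share of the detectable difference.** An expectation shift of, say, 0.3 to 0.5 points would have no source in the documents.

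**Conclusion.** The point holds as a minor inconsistency and a cheap improvement in design. The instruction conflicts with the Introduction and sits badly with the Discussion, and it raises expectation before a subjective outcome. Unequal action across arms is possible but not shown. It rests on the assumption that patients can perceive whether, and at which site, they are stimulated; Section 2.4.2 makes this plausible, though Section 2.2 describes patients as blinded. Neither size nor direction can be derived from the documents. The sample size and the planned analyses are unaffected.

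**What to change.** In Section 2.4.2.1.2, delete the reference to exact effects and put in its place one neutral briefing, worded identically for all patients and given before allocation is known. It should say that:

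- pads are placed at the ear and the arm;
- current may be given at the ear, at the arm or not at all;
- it may or may not be felt;
- it is not known whether either site or any mode reduces pain.

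Staff may still talk with patients as needed to set the current, but should not suggest benefit. Align the description of the control group in Section 2.4.2 with this wording.

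The cost is one paragraph of text. Patients receive a little less reassurance about the stimulation itself; general reassurance about the surgery can stay, the same for all. The change limits what patients can attach to a felt or unfelt current. It does not repair the sham contrast itself, which needs separate attention.

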###### 2.4.2.1.3 Relevant concomitant care permitted or prohibited during the trial

During the entire trial, subjects are required not to use any other analgesic measures or drugs, as this may affect the outcome.

### 2.5 Outcomes

#### 2.5.1 Primary observation indicators

•Bispectral index (BIS) to assess the depth of anesthesia.•Modified Observer’s Assessment of Alertness/Sedation Scale (MOAA/S) and Ramsay sedation scale to assess the sedation level of patients.•Visual Analogue Scale (VAS) to assess the pain level of patients.

Heart rate variability (HRV) is the variability of cycle-to-cycle differences in heart rate, which is mainly controlled by the autonomic nerves of the heart, and has been widely recognized as a valid indicator for assessing autonomic function. Heart rate is monitored and recorded using a three-lead ECG. We can use time-domain, frequency-domain, and non-linear measures to characterize HRV over 24 h, short-term or transient and ultrashort-term (24). Among the frequency-domain indices: the high-frequency component reflects parasympathetic regulation of heart rate (25), whereas the low-frequency component reflects sympathetic and parasympathetic actions (26). The ratio of low-frequency (LF) to high-frequency (HF) in HRV can be used as an indicator of cardiac autonomic balance, i.e., a decrease in the LF/HF ratio indicates a shift in cardiac autonomic balance toward parasympathetic dominance, which leads to an improvement in HRV (27). Time-domain metrics quantify the amount of change in interbeat interval measurements. Time domain analysis was recorded and analyzed from: AVNN, SDNN, RMSSD, SDANN, and NN50. For non-linear measurements the Poincaré plot was analyzed by fitting an ellipse. This resulted in three non-linear measurements, i.e., S, SD1, and SD2.

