## 3 Statistical analysis methods

### 3.1 Statistical methods for primary and secondary outcomes

This study will use SPSS 20.0 and PhysioZoo software for statistical analysis. The significance level of all statistical tests is set at α = 0.05, and two-sided tests are performed. For the differences in different intraoperative indicators such as pain score VAS, anesthesia depth BIS, and heart rate variability HRV between the trans-auricular vagus nerve stimulation group (taVNS group) and the transcutaneous peripheral nerve stimulation group (TENS group), an independent-samples *t*-test is first performed. If the data do not meet the normal distribution, the non-parametric test method Mann–Whitney U test will be used for comparison between the two groups. For the comparison between different subgroups (different stimulation modes) within each group, one-way analysis of variance will be performed to compare the differences in various indicators. If the data do not meet the assumptions of analysis of variance, the Kruskal–Wallis H test will be used as a non-parametric alternative method. At the same time, for multiple-measurement data, repeated-measures analysis of variance (Repeated Measures ANOVA) will be used to compare the changes of indicators at different time points within the same group. To further evaluate the impact of different influencing factors (such as stimulation mode) on intraoperative analgesia and sedation effects, multiple linear regression analysis will be used to help identify their relationships with various indicators.

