### 3.5 Expected results

The expected research results are that taVNS may exert sedative effects and potentially reduce the use of adjuvant analgesic drugs and has a positive effect on the relevant indicators of heart rate variability, which is a new and effective anesthesia-assisting method during foraminoscopy. The specific manifestations are as follows: 1. The taVNS group has a more obvious analgesic effect (the VAS score increases more significantly), a more obvious impact on the relevant indicators of HRV (the standard deviation of heart rate increases, RMSSD and SDNN decrease, and LF increases), a lower BIS value, and a significant reduction in the additional amount of oliceridine fumarate for patients compared with the TENS group. This indicates that the regulatory role of the vagus nerve plays an important role in pain regulation, and taVNS enhances the activity of the parasympathetic nerve, making the depth of anesthesia more stable; 2. TENS has a certain analgesic effect, but its impact on HRV is not significant; 3. Among different stimulation modes, the dense-sparse wave group (sparse wave 6 Hz, dense wave 30 Hz) has more obvious changes in HRV, VAS, BIS, and sedation under the parameters of 30 Hz and 200-pulse width. At the same time, by using the Huatuo brand electronic diagnosis and treatment instrument SDZ-IIB, a more effective and safer stimulation mode for the sedative and analgesic effects of patients can be obtained, providing more simple and effective treatment guidance for patients.

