This study explored the differences in the curative effects of TENS and taVNS in monitored anesthesia during foraminoscopy. The results of the study are expected to show that transcutaneous electrical nerve stimulation not only has a certain effect on sedation and analgesia, but also can reduce the use of auxiliary analgesic drugs and has a positive effect on the indexes of HRV, which is a new and effective anesthesia auxiliary modality in intervertebral foraminoscopy. The specific performance is as follows: 1. The taVNS group has a more obvious analgesic effect than percutaneous peripheral nerve stimulation, a more obvious effect on the relevant indexes of HRV (increase in the standard deviation of heart rate, increase in RMSSD, decrease in SDNN, and increase in LF), a significant decrease in the LF/HF ratio by taVNS, a change in the autonomic balance of the heart to a parasympathetic/vagal dominance, a significant decrease in the patient’s response to oxalidine fumarate, and a significant decrease in the amount of additional drugs, which can be shown to be a new and effective anesthetic aid in intervertebral foraminoscopy. The additional amount was significantly reduced, which can indicate that the modulation of vagus nerve plays an important role in pain modulation, and the taVNS enhanced the activity of parasympathetic nerves and stabilized the depth of anesthesia; 2. TENS had a certain analgesic effect, but its effect in HRV was not significant; 3. In different stimulation modes, the dense-sparse wave group (sparse wave 6 Hz-dense wave 30 Hz). Among the different stimulation modes, the sparse-dense wave group (sparse wave 6 Hz-dense wave 30 Hz) had more obvious changes in HRV, VAS, BIS, and sedation under the parameters of 30 Hz and 200 pulse width. At the same time, by using the electronic diagnostic instrument SDZ-IIB, it is possible to derive more effective and safer stimulation modes for patients’ sedation and analgesia, and to provide patients with simpler and more effective therapeutic guidance.

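### The trial is sized on VAS as its one primary outcome, but section 2.5.1 lists several unranked primary outcomes, all to be tested at 0.05

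*Protocol article*

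**What the plan says.** All places are in the protocol article.

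- **Section 2.3** bases the sample size on one outcome, "with the VAS as the primary outcome indicator", and adds that "the standard deviation of taVNS is 2.5, and that of TENS is 3.0". The result is 121 per group, raised to 136 for dropout, 272 in total.
- **Section 2.5.1**, the primary list, has bullets for "Bispectral index (BIS) to assess the depth of anesthesia", for MOAA/S and Ramsay, and for VAS. An unbulleted paragraph under the same heading describes HRV: five time-domain indices, LF, HF and their ratio, and three non-linear indices. Nothing is ranked. Section 2.5.2, the secondary list, does not contain HRV.
- **The abstract** gives a third list of main parameters. It omits Ramsay and adds oliceridine use, which appears in neither 2.5.1 nor 2.5.2.
- **Section 2.4.2.1 and Table 1** schedule VAS, BIS, MOAA/S, Ramsay and HRV at T1 to T8. T1 precedes stimulation, T2 precedes surgery, and T3 to T8 run from the start to the end of the operation.
- **Section 3.1** states: "The significance level of all statistical tests is set at α = 0.05", two-sided. It compares the two groups on intraoperative indicators by t-test or Mann–Whitney test, naming VAS, BIS and HRV as examples. Repeated-measures ANOVA is used only for change over time within a group.
- **Section 3.5** predicts: "The taVNS group has a more obvious analgesic effect (the VAS score increases more significantly", and for HRV "RMSSD and SDNN decrease, and LF increases". **Section 4** predicts "increase in RMSSD, decrease in SDNN, and increase in LF".

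**The concern.** A trial sized on one outcome should be decided by that outcome. Here the sizing section has one primary and the outcomes section has four scales plus HRV, with no order among them and the same 0.05 for each. If taVNS differed from TENS on BIS but not on VAS, the document gives no basis for calling the trial positive or negative. If any of the listed primaries can carry the conclusion, the chance of a false positive finding is well above the nominal 5%.

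The predicted directions add a smaller problem. VAS is defined in 2.5.1 as a measure of pain, so a VAS that rises more cannot describe better analgesia. RMSSD is given opposite expected directions in two sections.

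**Working it through.** **1. The plan's own figure.** Section 2.3 gives the two standard deviations but neither the difference nor the power, so 121 cannot be derived from the stated inputs alone. With an assumed difference of 1.0 point and two-sided 0.05:

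- Common SD = √((2.5² + 3.0²)/2) = √7.625 = 2.761.
- Unequal-variance t-test power is 80.1% at n = 121 and 79.8% at n = 120.

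So 121 matches one outcome, tested once, at 80% power, on that assumption.

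**2. Number of between-group tests.** The document does not fix it. Three counts bracket a reasonable reading:

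- the four bulleted scales at one time: 4 tests;
- the same with HRV counted as one further outcome: 5 tests;
- the four scales at each operative time, T3 to T8: 4 × 6 = 24 tests.

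Six times is used because section 3.1 speaks of intraoperative indicators.

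**3. Chance of at least one false positive if no outcome differs.** For k independent tests at 0.05 it is 1 − 0.95^k.

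| Reading | k | Independent |
|---|---|---|
| One outcome, one time | 1 | 5.0% |
| Four scales, one time | 4 | 1 − 0.95⁴ = 18.5% |
| Four scales and HRV, one time | 5 | 1 − 0.95⁵ = 22.6% |
| Four scales, T3 to T8 | 24 | 1 − 0.95²⁴ = 70.8% |

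The tests are correlated, so these are upper values. For the 24-test reading, multivariate normal test statistics were simulated (200,000 draws), with a common correlation between scales, a common correlation over time, and the product of the two for different scales at different times. The document gives no correlations, so these are assumptions.

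| Between scales | Over time | At least one false positive |
|---|---|---|
| 0 | 0.5 | 60.6% |
| 0.3 | 0.5 | 57.8% |
| 0.3 | 0.7 | 48.7% |
| 0.5 | 0.7 | 44.3% |

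**4. What keeping five primaries would cost.** At 80% power, n = 121 implies a difference of 2.761 × √(2/121) × (1.960 + 0.842) = 0.995. With Bonferroni, alpha per outcome is 0.05/5 = 0.01, and n = 2 × 7.625 × (2.576 + 0.842)²/0.995², which gives 181 per group. At 121 per group, power for VAS would be Φ(2.802 − 2.576), about 59%.

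**5. Predicted directions, side by side.**

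| Measure | Section 3.5 | Section 4 |
|---|---|---|
| VAS, for better analgesia | rises more | no direction given |
| RMSSD | falls | rises |
| SDNN | falls | falls |
| LF | rises | rises |
| SD of heart rate | rises | rises |

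Only RMSSD reverses between the sections. The VAS entry contradicts the definition of VAS in 2.5.1.

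**The case against.** The strongest reply is that an analysis plan, not shown here, would normally fix the time point and the multiplicity rule, and that a journal article condenses. Section 3.1 sets a level for tests; it does not say that any single significant result makes the trial a success. That stands as far as omissions go. It does not remove what is stated: one primary in 2.3, several in 2.5.1, and 0.05 for all tests. A later multiplicity rule would have to alter that last sentence.

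A second reply is that the number of tests is inferred. That also stands. Section 3.1 never says that a test is run at each time, and it does not name MOAA/S or Ramsay for the between-group test. The 24-test figures are therefore conditional; the single-time figures do not depend on repeated testing over time.

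A reader might infer more than the document supports:

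- *Testing at all eight times.* T1 is before stimulation and T2 before surgery, so six operative times is the likelier count.
- *A false positive is close to certain.* The correlated figures, 44% to 61%, do not show that. Treating every HRV index as its own primary test reads too much into a descriptive paragraph.
- *The 5% level holds for no claim.* A single VAS comparison keeps 5% once one time or summary is fixed.
- *Almost any HRV result could be called confirmation.* Only RMSSD reverses. SDNN and the standard deviation of heart rate are different quantities, so opposite predictions for that pair are not by themselves a contradiction.

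**Conclusion.** The concern holds in this form. The primary outcome in 2.3 and the primary list in 2.5.1 contradict each other, and section 3.1 applies 0.05 to every test without reducing the between-group comparison to one. The family-wise error is up to 19% for four scales at one time and up to 23% with HRV as one further outcome. If the four scales were tested at six operative times, it would be 71% under independence and about 44% to 61% under the assumed correlations. These figures assume that any listed primary could support the conclusion, which the document neither states nor excludes.

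The direction errors for VAS and RMSSD are real but secondary. All tests are two-sided, so no p-value changes; what is left unclear is which direction counts as benefit.

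**What to change.** 1. In 2.5.1, name VAS as the only primary outcome, as one pre-specified intraoperative summary compared between TENS and taVNS at two-sided 0.05. One option is the baseline-adjusted mean of the scheduled intraoperative values available for each patient, which also covers operations that end before the 2.0 h assessment.
2. Move BIS, MOAA/S, Ramsay and HRV to secondary, and bring the abstract's list into line.
3. In 3.1, confine the 0.05 level to the primary comparison. For the secondary outcomes, either apply Holm or a fixed sequence to a short list or label them exploratory.
4. Correct 3.5 and 4 so that lower VAS means better analgesia and RMSSD has one predicted direction.

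The cost is that secondary claims become harder to make. The 121 per group need not change on this account; its unstated difference and power are a separate matter.

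Whether the un-energised control subgroups enter the primary comparison is also separate and not part of this fix. Leaving them out would keep three of four subgroups, 3 × 32 = 96 to 3 × 34 = 102 per group before dropout (34 being 136/4). Power for a simple comparison would then be about 70% to 73% under the assumed 1.0-point difference, against 80% at 121. That choice needs its own power statement.

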##### 2.4.2.1 Observation indicators

Record the changes of corresponding indicators at different time points:

•Time 1: 5 min after the patient enters the operating room, before electrical stimulation.•Time 2: Before the operation, 30 min after the electrical stimulation upon entering the room.•Time 3: Immediately at the start of the operation.•Time 4: 0.5 h after the start of the operation.•Time 5: 1.0 h after the start of the operation.•Time 6: 1.5 h after the start of the operation.•Time 7: 2.0 h after the start of the operation.•Time 8: At the end of the operation.

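### SDANN is listed as a per-time-point HRV index although the schedule leaves it uncomputable in short windows and imprecise in longer ones; NN50 is better reported as pNN50

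*Protocol article*

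**What the plan says.** All references are to the protocol article.

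- Section 2.5.1 places HRV under the primary observation indicators and gives the time-domain list: "Time domain analysis was recorded and analyzed from: AVNN, SDNN, RMSSD, SDANN, and NN50". It names no pNN50 and does not define the indices.
- The same section says in general terms that one can use "measures to characterize HRV over 24 h, short-term or transient and ultrashort-term". It does not say which of these recording lengths applies in this trial.
- Section 2.4.2.1 sets the schedule: "Record the changes of corresponding indicators at different time points". T1 is "5 min after the patient enters the operating room, before electrical stimulation", T3 is "Immediately at the start of the operation" and T4 is "0.5 h after the start of the operation". T5 to T7 follow at half-hour steps, and T8 is the end of the operation.
- Table 1 (Section 2.5.3) marks HRV at every point from T1 to T8.
- Section 3.1 compares HRV between the taVNS and TENS groups and uses repeated-measures ANOVA for change over time within a group.
- Section 1 expects taVNS to lower heart rate.

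**The concern.** SDANN was designed for long recordings. It describes slow drift between 5-minute blocks, so it needs several blocks. The plan as written applies it at time points that are at most half an hour apart during surgery, with a baseline taken 5 minutes after room entry. If the baseline value does not exist, change from baseline cannot be analysed. If later values rest on two to six blocks, each patient's value is very noisy.

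NN50 raises a smaller issue. It counts successive NN differences above 50 ms, so it grows with the number of beats recorded. If taVNS slows the heart, the count falls for that reason alone, even when the share of large differences is unchanged. That is an arm-related shift that has nothing to do with the quantity of interest.

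Both indices sit under the primary heading and would be tested between groups and over time.

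**Working it through.** The plan gives no figure for these indices, so there is nothing to reproduce. The check asks what the stated schedule allows.

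**Inputs from the article.** Eight time points with HRV at each (Section 2.4.2.1, Table 1); T1 at 5 minutes after room entry; 30-minute spacing from T3 to T7; 136 patients per group and 32 per subgroup (Section 2.3).

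**Assumptions.** SDANN = SD of the means of consecutive 5-minute NN segments. NN50 = count of successive NN differences above 50 ms. Segment means are independent and normal for the interval calculation.

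**Step 1: SDANN.** A window of w minutes holds k = floor(w/5) segments. An SD from k values has k − 1 degrees of freedom, so its 95% interval runs from √[(k−1)/χ²(0.975; k−1)] to √[(k−1)/χ²(0.025; k−1)] times the estimate. Its coefficient of variation (CV) is √(1 − c₄²)/c₄, with c₄ = √[2/(k−1)] · Γ(k/2)/Γ((k−1)/2).

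For k = 6: √(5/12.83) = 0.62 and √(5/0.831) = 2.45.

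| Window | Segments k | 95% interval (× estimate) | CV |
|---|---|---|---|
| 5 min or less | 0 or 1 | undefined | – |
| 10 min | 2 | 0.45 to 31.9 | 76% |
| 15 min | 3 | 0.52 to 6.28 | 52% |
| 20 min | 4 | 0.57 to 3.73 | 42% |
| 30 min | 6 | 0.62 to 2.45 | 32% |
| 2 h (whole recording) | 24 | 0.78 to 1.40 | 15% |
| 24 h | 288 | 0.92 to 1.09 | 4% |

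If the T1 window ends at T1, it holds at most 5/5 = 1 segment, so SDANN is undefined there. From T3 to T7, windows that do not overlap hold at most 30/5 = 6 segments.

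**Step 2: what this does to a group mean.** The noise of individual estimates averages out. At six segments it adds about 32%/√136 = 2.7% to the standard error of a group mean, and 32%/√32 = 5.7% for a subgroup. Averaging does not help where the index is undefined.

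**Step 3: NN50.** Expected NN50 = pNN50 × (beats − 1). Take pNN50 = 10% and a fixed 5-minute window:

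- 80 beats/min: 0.10 × (400 − 1) = 39.9
- 60 beats/min: 0.10 × (300 − 1) = 29.9

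The count falls by 10.0/39.9 = 25% while pNN50 stays at 10%. The two heart rates are illustrative and not an expected treatment effect.

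**Step 4: how much of NN50 is recording length?** The variance of log expected NN50 was split into window length, heart rate and pNN50. The assumed spreads are a log-SD of 0.7 for pNN50 around 8%, and a heart rate of mean 75 and SD 10.

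| Window across recordings | Share from window | Share from heart rate | Share from pNN50 |
|---|---|---|---|
| fixed at 5 min | 0% | 4% | 96% |
| 4 to 6 min | 3% | 4% | 94% |
| 2 to 10 min | 27% | 3% | 70% |
| 1 to 30 min | 54% | 2% | 45% |

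With equal windows NN50 is close to a rescaled pNN50, with a small heart-rate component.

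**The case against.** Several stronger readings are tempting, and the article does not support them.

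- **That NN50 mainly reflects recording length, or cannot be compared between T1, T3 and T8.** This needs windows that differ widely. The article neither fixes the window nor says that it varies, and the full protocol may well fix it. Its absence from a condensed article is not a finding. With equal windows the counts are comparable apart from the heart-rate component.
- **That baseline SDANN is undefined whatever is done.** This assumes that the window ends at T1. Section 2.4.2.1 gives a time label, not a recording interval, and a window running forward from T1 is possible if stimulation starts late enough. The same holds for T3: the start of surgery is a label, not a recording of zero length.
- **That the tests carry no valid signal.** At six segments the noise is large for one patient but modest for a group mean (Step 2). The arms follow the same schedule, so recording length alone should not create a systematic difference between them.

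A fair defence is also that SDANN might be meant once per patient over the whole recording. Table 1 marks HRV as a block, not each index. In a 2-hour recording there would be 24 segments and a CV of about 15%, which is usable. But the article does not say this. Its list of indices, its schedule and its repeated-measures analysis together describe HRV per time point.

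What stands after these objections is that SDANN does not suit the per-time-point use described, and that pNN50 is a better choice than a raw count.

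**Conclusion.** The point holds in a limited form. Given the conventional 5-minute segment, per-time-point SDANN cannot be computed in windows of 5 minutes or less, including T1 if the window ends there. It is imprecise in every non-overlapping intraoperative window; even the longest leaves an individual 95% interval of 0.62 to 2.45 times the estimate, assuming independent normal segment means. This part does not depend on knowing the actual window length.

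For NN50 the conclusion is only that the count carries a heart-rate component, in a trial where one arm is expected to slow the heart, and a recording-length component if windows differ.

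The consequence is minor. These are two of many HRV indices, VAS is the outcome behind the sample size (Section 2.3), and the expected results in Sections 3.5 and 4 name other HRV measures (SD of heart rate, RMSSD, SDNN, LF and, in Section 4, LF/HF). No stated conclusion rests on SDANN or NN50.

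**What to change.** In Section 2.5.1, remove SDANN from the indices evaluated at each time point, or state that it is computed once per patient over the whole recording and kept out of the repeated-measures analysis. Replace NN50 with pNN50, the share of successive NN pairs that differ by more than 50 ms, taken from the same ECG. AVNN, SDNN and RMSSD can stay as listed.

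This is a change of wording. It needs no new recordings, patients or equipment. The small downside is that one listed index is lost, or is reported only once per patient.
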